### Sample size calculation

Based on reviews on electronically-delivered programs for the prevention of addictive disorders [25–29], we expect a small effect size for the main outcome of this study, the non-parametric composite measure of addictive behaviours. Based on an expected Cohen’s d of 0.2, a sample size of *n* = 412 in each study group would be required to have 80% power for a Wilcoxon-Mann-Whitney-test (α = 5%, 2-sided) in order to detect this difference based on a calculation using G-Power. As vocational school students are nested within school classes, we additionally need to consider a potential design effect for the calculation of the sample size for our study. Based on previous efficacy studies in vocational schools [6, 19], an average cluster size of 13 study participants per school class and an intra-cluster correlation coefficient of 0.05 could be expected. This would result in a design effect of 1.60. Multiplying this design effect by the required size for an unnested sample (n = 412) results in a required sample size of *n* = 659 per study group and a total of *n* = 1318 study participants. Thus, based on the participation rates of previous efficacy studies among vocational school students [19, 21], approximately 100 school classes are required to reach this sample size.

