**Methods/design:**

The efficacy of the *ready4life* coaching program will be tested in comparison to an assessment only control group, within a cluster-randomised controlled trial with one follow-up assessment after 6 months. At the beginning of the program, participants of the intervention group will receive an individual profile, showing areas in which they have sufficient resources and in which there is a need for coaching. Based on this feedback, they can select two out of the following six program modules: stress, social skills, Internet use, tobacco/e-cigarettes, cannabis, and alcohol. Participants of the intervention group will receive individualised coaching by a conversational agent (chatbot) for a period of four months. The coaching relies on motivational and social-cognitive principles of behaviour change. Within weekly dialogues, the coach provides individually tailored information in different formats, such as videoclips, texts, or pictures. Study participants will be 1318 apprentices with a minimum age of 15, recruited in approximately 100 vocational school classes in Switzerland. Primary outcome will be a composite measure for addictive behaviours including (1) at risk-drinking, (2) tobacco/e-cigarette smoking, (3) cannabis use, and (4) problematic Internet use.

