Subsequently, participants of intervention classes will receive an individual profile on their risks and resources and can select two topics (stress, social skills, Internet use, tobacco, cannabis, and alcohol) on which they will receive coaching, for a period of four months (two months per topic) by the chatbot. Participants of the assessment only control classes will not receive the intervention program. However, they will be invited to participate in the program after completion of the follow-up assessment in month 6. Follow-up assessment will be conducted in both study groups using a similar procedure: participants will be invited to complete the online follow-up assessments via SMS text messaging. Non-responders will additionally be addressed via computer-assisted telephone interviews conducted by research assistants.

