### Data analyses

Generalized Linear Mixed Models will be used to test intervention effects for binary and count outcomes and Linear Mixed Models for continuous outcomes [38, 39]. These models account for both fixed and random effects and are particularly useful in analysing longitudinal and nested data (e.g., students within school classes). To test the efficacy of the intervention, we will test the variables “study group”, “time” and their interaction “study group x time” as predictors of the outcome criteria assessed at follow-up. If necessary, we will control baseline differences by adding additional baseline variables as covariates to the models. We will conduct both (1) intention to treat analyses and (2) complete case analyses considering all study participants with available follow-up data. For ITT analyses, we will use multiple imputation procedures as described elsewhere [40].

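### The 1318 needed with outcome data is also the number to be recruited, so the stated 80% power for the Wilcoxon-Mann-Whitney test assumes complete six-month follow-up

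*Protocol article*

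**What the plan says.** The Sample size calculation section gives the whole chain. It starts from the effect size ("Based on an expected Cohen’s d of 0.2") and finds that 412 per group "would be required to have 80% power" with a two-sided Wilcoxon-Mann-Whitney test at 5%. It then takes an average of 13 participants per class and an intra-cluster correlation of 0.05, which give a design effect of 1.60. The last step reads: "Multiplying this design effect by the required size for an unnested sample (n = 412) results in a required sample size of" 659 per group, or 1318 in total. Participation rates in earlier studies turn 1318 into about 100 classes.

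The Abstract (Methods/design) uses the same number for enrolment: "Study participants will be 1318 apprentices with a minimum age of 15", to be recruited in about 100 classes.

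Two other sections expect missing follow-up. Under Participants, setting and procedure: "Non-responders will additionally be addressed via computer-assisted telephone interviews conducted by research assistants". Under Data analyses, the plan includes multiple imputation for the intention-to-treat analysis, and also "complete case analyses considering all study participants with available follow-up data".

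**The concern.** A power calculation for a two-sample test counts people whose outcome is observed. Here that count is multiplied by the design effect and by nothing else, and the result becomes the recruitment target. One figure therefore serves as both the number analysed and the number enrolled, which is consistent only if every recruit provides six-month data. The plan's own procedures show that its authors do not expect this.

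At stake is how the primary result will be read. The expected effect is small, so a null finding would be taken as coming from a trial with 80% power for d = 0.2. The calculation as given supports that figure only with no loss.

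**Working it through.** **Inputs from the Sample size calculation section:** d = 0.2, two-sided α = 0.05, power 80%, 412 per group before clustering, 13 participants per class, ICC 0.05.

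**Reproducing the plan's figure**
- Two-sample t-test: 393.4 per group.
- Divide by the asymptotic relative efficiency of the Wilcoxon-Mann-Whitney test under normality, 3/π = 0.955: 393.4 / 0.955 = 412.0.
- Design effect: 1 + (13 − 1) × 0.05 = 1.60.
- 412 × 1.60 = 659.2, so 659 per group and 2 × 659 = 1318.
- 1318 / 13 = 101.4, which matches the roughly 100 classes.

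Every step reproduces, and 1318 is reached without an attrition term. With 1318 analysed, power is 80.0%.

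**Power if 1318 are recruited and a fraction f is followed up.** The documents give no f, so the values below are assumptions.
- Observed per group: 659f.
- Case A, in which loss also shrinks the observed classes: m = 13f, DE = 1 + (13f − 1) × 0.05.
- Case B: DE held at 1.60.
- Effective number per group: n_eff = 659f / DE.
- Power ≈ Φ(0.2 × √(n_eff × 0.955 / 2) − 1.96). The tabulated values use the t-based version, which differs by less than 0.2 percentage points in the Case A rows.
- Detectable d at 80% power: 0.2 × √(412 / n_eff).

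Worked example, f = 0.8, Case A: 659 × 0.8 = 527; m = 10.4; DE = 1 + 9.4 × 0.05 = 1.47; n_eff = 527.2 / 1.47 = 359; 0.2 × √(359 × 0.955 / 2) = 2.62; 2.62 − 1.96 = 0.66; power about 74%.

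| Follow-up (assumed) | Observed per group | DE (A) | n_eff (A) | Power (A) | Detectable d (A) | Power (B, DE 1.60) |
|---|---|---|---|---|---|---|
| 100% | 659 | 1.60 | 412 | 80.0% | 0.20 | 80.0% |
| 90% | 593 | 1.535 | 386 | 77.4% | 0.21 | 75.7% |
| 80% | 527 | 1.47 | 359 | 74.3% | 0.21 | 70.7% |
| 70% | 461 | 1.405 | 328 | 70.6% | 0.22 | 64.9% |

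A loss of only 5% gives 78.8% (A) or 77.9% (B). Case A is the natural one when dropout is spread across classes.

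**The case against.** **The plan works to limit loss.** It offers 10 CHF for completing follow-up, invites participants by SMS and telephones those who do not respond. This stands, and it bears on how large the loss will be. It does not make the loss zero, and no expected rate is given.

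**The 13 per class could already be net of dropout.** The text does not fit this. The step from 1318 to about 100 classes rests on participation rates, and the Abstract describes the 1318 as recruited.

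**Multiple imputation keeps everyone in the analysis.** It keeps them in the analysis set, but it restores information on a missing outcome only as far as the observed data predict it.

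**The planned mixed model uses baseline data and may recover the power.** This is the strongest objection, and part of it stands: the primary analysis is not the unadjusted test used for sizing, so its power could be higher than the table shows. A reader might infer that the shortfall therefore disappears. The documents do not support that. They give no baseline correlation, and any gain depends on the model. Adjusting the follow-up value for baseline multiplies the variance by 1 − ρ²; an unconstrained group-by-time contrast, which is what Data analyses describes, is in essence a comparison of changes, with factor 2(1 − ρ). At an assumed ρ of 0.5 these are 0.75 and 1.0, so the second gives no gain at the same ICC. Removal of stable class effects could improve it, but no ICC for change is given either.

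**The size is modest.** This also stands. In Case A the drop is 3 to 9 percentage points over the assumed range, small beside the uncertainty in an expected d of 0.2.

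**Conclusion.** The point holds as a stated power that the design does not deliver, and it is of moderate severity. For the unadjusted Wilcoxon-Mann-Whitney test at d = 0.2, 1318 recruited gives 80% power only with complete follow-up. The direction is certain for any loss above zero. The size rests on assumed follow-up of 90%, 80% and 70%: about 77%, 74% and 71% if the design effect falls with class size, and 76%, 71% and 65% if it is held at 1.60. The detectable effect in the first case is about d = 0.21 to 0.22.

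Three stronger readings are tempting and are not supported.
- A reader might infer an arithmetic error. Every step shown is correct; an attrition step is absent.
- A reader might infer that the planned primary analysis has less than 80% power. The figures above are for the test used in sizing. The power of the mixed model cannot be derived from what the article gives, in either direction.
- A reader might add a further loss for unequal class sizes. The article calls 13 an average and gives no measure of spread, so any such figure would be invented, and using the average is a common simplification.

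**What to change.** Reword the Sample size calculation section so that the recruited and analysed numbers are distinct, for example: 1318 recruited; at an expected follow-up of X%, power for d = 0.2 is Y%. Alternatively, give the effect detectable with 80% power at that follow-up. X should come from the sponsor's own experience in comparable school studies, and the text should say whether the design effect is recalculated for the smaller observed classes.

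If the sponsor wishes to claim a gain from baseline data, it should be computed for the group-by-time model described in Data analyses, with the assumed baseline correlation stated.

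This changes the stated power and does not ask for more participants. The cost is a few sentences and a slightly less favourable figure for the Wilcoxon-Mann-Whitney test.

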### Intervention program

*ready4life* (www.r4l.swiss) is a smartphone application-based addiction prevention program for adolescents that takes into account the heterogeneity of adolescent addictive behaviour by promoting life skills on the one hand and reducing risk behaviours on the other. The program provides individually tailored coaching by a conversational agent (chatbot, see Fig. 2).

**Fig. 2 Fig2:**
[figure not shown]
Screenshots from the *ready4life* coaching program (left: selection of avatar, right: sample chatbot dialogue)

After choosing a male or female avatar, participants are invited by the chatbot to provide demographic data (age and sex) and to complete the baseline assessment on stress, self-efficacy, social skills, Internet, tobacco/e-cigarette, cannabis, and alcohol use. Subsequently, an individual feedback is generated on the basis of this survey conducted via smartphone. Using the traffic light colours, this feedback shows areas in which a participant has sufficient resources and in which there is a need for coaching or counselling. Based on this feedback, participants can select two out of the following six program modules: stress, social skills, Internet use, tobacco/e-cigarettes, cannabis, and alcohol. Using the individual data from the baseline assessment, participants receive coaching for a period of 8 weeks for each of the two selected topics. During this 4-month coaching the virtual coach motivates the participants to deal sensibly with addictive substances, gives feedback on current consumption and life skills, and provides individually tailored information in weekly dialogues. Participants are notified of a new module every Tuesday via push message. The time required to process a weekly dialog is between two and five minutes. Participants can also start a conversation with the chatbot themselves by selecting one of several predefined topics within each module (e.g. “quiz on myths about alcohol” within the alcohol module or “using body language effectively” within the module on social skills). In a separate chat within the app (“Ask the Expert”) the participants can pose personal questions to regional addiction prevention experts. Young people with high-risk addictive behaviour are encouraged to seek further advice (e.g., regional outpatient counselling services). In order to stimulate active program engagement, several interactive elements such as quiz questions, contests and a playful competition are integrated into *ready4life*. Program users can collect credits for each completed weekly dialogue with the chatbot. The more credits participants will collect, the higher their chances will be of winning one of several attractive prizes which will be part of a prize draw after program completion. Participants will be able to retrieve their number of credits compared to the number of credits of other program participants’ of their group (similar starting date) at any time from an individual profile page.

Each program module has a similar structure (Table 1) and contains similar intervention elements based on principles of the Social-Cognitive Theory (e.g., goal-setting, self-monitoring, observational learning) [30], the Social Norms Approach (e.g., normative feedback) [31] and Motivational Interviewing (e.g., decisional balance) [32].

**Table 1 Tab1:** Coaching contents and elements of ready4life: similar structure for each of the six modules on stress, social skills, Internet use, tobacco/e-cigarettes, cannabis, and alcohol

Week	Objective	Example: tobacco/e-cigarettes	Scientific principle
1	Getting individual feedback	Feedback on smoking costs Smoking prevalence in reference group	Self-Monitoring Normative Feedback
2	Realizing risks Motivation to improve skills	Pros and cons of smoking and smoking cessation	Decisional balance Outcome expectations
3	Learning from other participants	Picture Contest “What could help you or others to become smoke-free?”	Observational Learning Facilitation
4	Creating if-then behavior plan	If-then-plan for dealing with temptation in smoking situations	Implementation Intention Self-Regulation
5	Clarifying individual questions	Possibility to ask an expert on smoking and smoking cessation	Facilitation
6	Selecting and pursuing a personal goal	Personal challenge on the subject of smoking	Goal-setting Self-Monitoring
7	Learning to deal with difficult situations	Video quiz on the social norm of smoking in children Motivation to resist peer pressure	Observational Learning Self-Efficacy
8	Broadening one’s own perspective	Summary of frequently asked questions and expert answers	Observational Learning Self-Efficacy

### Assessments and outcomes

At baseline, we will assess individual demographic variables (age, sex) as well as characteristics of the schools and school classes (type of vocational school, class size, apprenticeship profession, number of students present within school class). Baseline- and follow-up assessment will include the following addictive behaviours and life skills addressed in the intervention program:
At risk-drinking in the preceding 30 days, according to guidelines of the Swiss Federal Office of Public Health [33].30-days point prevalence for tobacco/e-cigarette smoking, according to the criteria of the Society for Nicotine and Tobacco Research [34].30-days point prevalence for cannabis use.Problematic Internet use assessed by the Short Compulsive Internet Use Scale [35].General self-efficacy assessed by the Short Scale for Measuring General Self-efficacy Beliefs [36].Stress assessed by a single-item measure of stress symptoms [37].

The primary outcome of the planned study is a composite measure (range: 0–4) for addictive behaviours, reflecting the number of risk behaviours (at-risk drinking, tobacco/e-cigarette smoking, cannabis use, problematic Internet use) that a person displays. Secondary outcomes are metric measures reflecting (1) alcohol use, (2) tobacco/e-cigarette use, (3) cannabis use, (4) problematic Internet use as well as (5) general self-efficacy [36] and (6) stress [37].

### Data analyses

Generalized Linear Mixed Models will be used to test intervention effects for binary and count outcomes and Linear Mixed Models for continuous outcomes [38, 39]. These models account for both fixed and random effects and are particularly useful in analysing longitudinal and nested data (e.g., students within school classes). To test the efficacy of the intervention, we will test the variables “study group”, “time” and their interaction “study group x time” as predictors of the outcome criteria assessed at follow-up. If necessary, we will control baseline differences by adding additional baseline variables as covariates to the models. We will conduct both (1) intention to treat analyses and (2) complete case analyses considering all study participants with available follow-up data. For ITT analyses, we will use multiple imputation procedures as described elsewhere [40].

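### The efficacy model's time and group-by-time terms cannot be estimated from a single follow-up; the stacked model probably meant gives up precision that prespecified baseline adjustment would keep at no cost

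*Protocol article*

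**What the plan says.** The protocol article's Data analyses section plans generalized linear mixed models for binary and count outcomes and linear mixed models for continuous ones. To test efficacy it enters study group, time and the group-by-time interaction "as predictors of the outcome criteria assessed at follow-up". Further baseline variables may be added as covariates if baseline differences make this necessary. The baseline value of the outcome itself is not named as a fixed covariate.

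The Abstract describes testing "within a cluster-randomised controlled trial with one follow-up assessment after 6 months", and Design and hypotheses gives the same schedule: baseline and 6 months. Assessments and outcomes states that the addictive behaviours are measured on both occasions. The primary outcome is a count, from 0 to 4, of risk behaviours.

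The Sample size calculation has "80% power for a Wilcoxon-Mann-Whitney-test", inflated by a design effect for classes. It is a two-group comparison and uses no baseline information.

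**The concern.** The sentence defining the efficacy test points two ways. Its response is the follow-up value, and baseline variables may be covariates, which fits a model of the 6-month outcome. Its predictors include time and group by time, which make sense only when both occasions are responses. With follow-up rows alone, time does not vary and the interaction duplicates group.

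Under the stacked reading, three terms are listed as testing efficacy but only one does so. With baseline as the reference occasion, the group term is the chance difference between arms before any intervention, and the time term is the change in controls. That leaves the interaction, a difference in mean change.

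At stake are a clear statement of the primary test and some precision. The baseline outcome is collected anyway. Using it as a covariate, rather than subtracting it, extracts more information at the planned cluster structure. The conditional covariates do not recover this, because in the stacked model the baseline outcome is already part of the response.

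**Working it through.** **1. The plan's own figure.** Inputs are from the Sample size calculation: "Based on an expected Cohen’s d of 0.2", 80% power, two-sided 5%, "an average cluster size of 13 study participants per school class", and "an intra-cluster correlation coefficient of 0.05 could be expected".

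- A two-sample t-test needs 394 per arm. A Wilcoxon-Mann-Whitney test with efficiency 3/π needs 412, as stated.
- Design effect: 1 + (13 − 1) × 0.05 = 1.60.
- 412 × 1.60 = 659.2, so 659 per arm and 1318 in total. The plan's figure reproduces.

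**2. Estimability.** On follow-up rows only, the design matrix (intercept, group, time, group by time) has four columns and rank 2. With baseline and follow-up stacked, the rank is 4. In a simulated linear mixed model (r = 0.5) the stacked interaction equalled the difference in mean change (−0.2888 both ways, standard error 0.0557 both ways). On the same data the baseline-adjusted standard error was 0.0489.

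**3. Variance factors with clustering.** Let ρ = 0.05 and m = 13 (plan), c = correlation of class effects between occasions (assumed), and r = within-class correlation between a student's baseline and follow-up values (assumed). The correlation between a class's baseline and follow-up means is

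R = [mρc + (1 − ρ)r] / [1 + (m − 1)ρ] = (0.65c + 0.95r) / 1.60.

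Subtracting b times the baseline mean from the follow-up mean gives, relative to follow-up alone, F(b) = 1 + b² − 2bR.

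- Follow-up only: b = 0, F = 1.
- Group by time (change): b = 1, F = 2(1 − R).
- Adjusted for the student's baseline, with a class random intercept: b ≈ r, F = 1 + r² − 2rR.
- Adjusted also for the class mean of the baseline: b = R, F = 1 − R².

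The adjusted analysis beats the change contrast when R < (1 + r)/2. At ρ = 0.05 and m = 13, even with c = 1, R = 0.406 + 0.594r, which is below 0.5 + 0.5r for every r < 1. The adjusted analysis also never does worse than follow-up alone: that needs R > r/2, and R is at least 0.594r when c ≥ 0 and r > 0.

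**4. Power.** Effective n per arm is 659/1.60 × 3/π = 393.3. The noncentrality is 0.2 × √(393.3/2) = 2.805, and power = Φ(2.805/√F − 1.96). With F = 1 this is 80%, as planned.

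| c | r | R | F, interaction | F, adjusted | Ratio | Power, interaction | Power, adjusted |
|---|---|---|---|---|---|---|---|
| 0.5 | 0.4 | 0.441 | 1.119 | 0.808 | 1.39 | 76% | 88% |
| 0.5 | 0.5 | 0.500 | 1.000 | 0.750 | 1.33 | 80% | 90% |
| 0.5 | 0.6 | 0.559 | 0.881 | 0.689 | 1.28 | 85% | 92% |
| 0.8 | 0.4 | 0.563 | 0.875 | 0.710 | 1.23 | 85% | 91% |
| 0.8 | 0.5 | 0.622 | 0.756 | 0.628 | 1.20 | 90% | 94% |
| 0.8 | 0.6 | 0.681 | 0.638 | 0.543 | 1.18 | 94% | 97% |
| 0.9 | 0.4 | 0.603 | 0.794 | 0.678 | 1.17 | 88% | 93% |
| 0.9 | 0.5 | 0.663 | 0.675 | 0.588 | 1.15 | 93% | 96% |
| 0.9 | 0.6 | 0.722 | 0.556 | 0.494 | 1.13 | 96% | 98% |

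Over r from 0.2 to 0.7 and c from 0 to 1, the ratio runs from 1.05 to 1.78. The interaction falls below the planned 80% only where R < 0.5.

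**The case against.** The strongest reply is that the sentence is loosely worded but its meaning is plain. Outcomes are measured twice, the section recommends mixed models for longitudinal data, and a two-occasion model with the interaction as efficacy contrast is a valid estimator under randomisation. Preferring baseline adjustment is then a question of efficiency, and its size rests on two correlations the article does not give. This largely stands. It lowers the priority of the point but does not remove it: the wording still contradicts the schedule, and the efficiency gain costs nothing.

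A reader might draw four stronger conclusions that the document does not support.

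- *The primary analysis cannot be carried out.* It can, once baseline is treated as a response. Only the literal wording fails.
- *A change contrast is always less precise.* This holds at the planned intra-cluster correlation, not universally. Stable class effects cancel in change scores. With c = 1 and 13 per class, the interaction becomes the more precise when 13ρ/(1 + 12ρ) exceeds 1/2, that is, when ρ exceeds 1/14, about 0.07 (against adjustment for the individual baseline only).
- *The trial is underpowered or its sample size wrong.* The figures reproduce, and in most of the tabulated range the interaction has at least the planned 80%.
- *The type I error is inflated because class-level variation in change is not modelled.* The article names students within classes only as an example of nesting, so the random-effects structure is not fixed here. The direction of any error also depends on it. A class intercept alone ignores the pairing within students and is conservative. A student effect without class by time would be anti-conservative.

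**Conclusion.** The point holds as a should-fix and a free improvement. Read literally, the sentence specifies terms that one follow-up cannot estimate. Read as a stacked model, it lists two terms that do not measure efficacy and one that does, and that one is less precise than a prespecified baseline-adjusted comparison at the plan's own ρ and class size. For r of 0.4 to 0.6, the likely gain is about 2 to 6 percentage points of power if class effects are fairly stable (c of 0.8 to 0.9), and about 7 to 12 if c is 0.5.

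The variance factors assume equal variances on the two occasions. They are exact for linear models and approximate for the 0–4 count and the binary outcomes. That the change contrast is less precise at the planned ρ is secure within the linear model; the size of the loss depends on r and c, which are assumptions.

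**What to change.** Replace the sentence on the three predictors with text such as: *The intervention effect is the coefficient of study group in a mixed model for the outcome at 6 months, with the baseline value of that outcome as a prespecified covariate, school (stratum) in the model and a random intercept for school class; this coefficient is the single primary test.* Drop the time and group-by-time terms.

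Adding the class mean of the baseline outcome as a second covariate protects precision if class effects prove stable. An equivalent alternative keeps the stacked layout, constrains the baseline means to be equal between arms, includes student and class random effects, and names the group difference at 6 months as the test.

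The cost is one sentence. No new data are needed, the sample size stands, and participants without follow-up enter through the multiple imputation already planned.
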